#### Preparing educators

Prior to the intervention ten female CHVs, aged from 27 to 53 years were trained in three workshops by a general practitioner. These subjects were selected from among fifty CHVs connected to a health delivery center (Sameno-al-aemaeh) in Kermanshah. The inclusion criteria were; an acceptable level of conversation skills, ability to speak in Persian and Kurdish, having been actively involved during the preceding year in assisting at the health center and having graduated from high school or beyond. Three one-day workshops were held to train and prepare the selected CHVs, the number and duration of workshops being based on a needs-assessment conducted at the introductory session and using the feedback from participants (CHVs) after that session.

The aim of workshops was to teach the CHVs about the content of the educational programs for patients and how to present the information. The materials were obtained from heart failure text books (Bonow et al.
2011) and related sites (Krum et al.
2011) that have been translated into simple Persian language understandable for patients, even those who might be illiterate. The preparation and simplification was conducted under supervision of a cardiologist. The information was provided in a PowerPoint presentation and in a notebook used in workshops. In addition, during workshops, tutors considered the likely questions or challenging issues that might be faced during their home visits. At the end of the workshops, using role play, each of CHVs was assessed to evaluate her ability as an educator. One of CHVs who did not have an acceptable result was removed from the list. Further, CHVs were given a contact number of a trained general practitioner to ask questions during home visits.

For the second group a nurse and general practitioner both experienced and working in cardiovascular disease and cardiovascular rehabilitation were employed. They were asked to study the notebook prepared as above. They were asked to educate participants, using their own knowledge and considering the aims and objectives of education. They were blind to the study purpose.

#### Payments

The interventions were started in parallel, though educating by CHVs lasted about two weeks because each CHV had to educate approximately seven to eight patients one-by-one and at their homes. The patients in second group –educated at hospital– were offered reimbursement for travel costs but none asked. Fees were paid to educators of this group, namely, the nurse and general practitioner. CHVs making home visits were reimbursed for travel costs. Taxi fares were paid for one of the investigators who monitored the home-based education. Two months later participants in the three groups were interviewed again at home or hospital, according to their preferences.

### Outcomes

The self-care components including self-care maintenance, self-care management and self-care confidence would be the main outcome variables of the study. These outcomes will be assessed before intervention and two months after intervention. The Persian version of the self-care chronic heart failure index V 6.2 (pSCHFI) scales is used to evaluate self-care components in three groups of study. The SCHFI uses a quantitative, ordinal, self-report and performance-rating scale (Riegel et al.
2009). Both SCHFI and pSCHFI include three scales with 22 questions–10 questions for self-maintenance, six for self-management and six for self-confidence. Each sub-scale is standardized to a possible score of zero to 100. In Persian version of SCHFI, in comparison with the original SCHFI, some grammatical changes had been made and a few words had been deleted or added, however none of those modifications did not change the meaning of the questions. For example, we inserted the phrase "How routinely do you…" at the beginning of many questions of the Self-maintenance sub-scale, instead of using only one sentence at the beginning of subscale, as used in the original SCHFI. In addition, item 4, "Do some physical activity?" was changed to "Do you routinely do your normal life activities such shopping and cleaning?" (Riegel et al.
2009; Siabani et al.
2014).

In order to obtain demographic data and personal health information- as the secondary outcomes-, an investigator-constructed questionnaire has been also administered that included 13 questions about age, sex, living status (with whom they live), smoking, co-morbidities (e.g. hypertension), duration of heart failure, and the number of times a patient had been admitted to hospital due to CHF symptoms from diagnosis CHF. This information will be used to evaluate the likely association between self-care scales and personal characteristics. Data collected by three experienced trained nurses and through interviewing have been conducted at the patient’s home or hospital, according to participant preference, before intervention and two months after intervention.

### Sample size

According to the following formula and information received from another study of a similar design (Riegel et al.
2009), it was expected the mean increase in self-care would be about 22 units (d = 22).

Hence to have a power of 90% (σ =40, d = 22, Z α/2 = 1.96, Z β =0.1) minimum 60 participants were needed for each group.

Considering a non-response rate of 15%, the sample size for each group would be 60, and total of 180 participants. However, according expert opinions, all 231 patients who had completed the primary interviews conducted to obtain the baseline data, and agreed with remaining in the study were considered to participate in the RCT, therefore, each group would be included 77 patients (Figure 
1).

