#### Primary objectives

To determine baseline self-care (self-care maintenance, self-care management and self-care confidence) in patients with CHF discharged from Imam Ali hospital (Iran) from August 2010 to June 2012.

To measure the scores relating to self-care (self-care maintenance, self-care management and self-care confidence) in each of the three arms of the study, two months after applying interventions.

To compare self-care maintenance, self-care management and self-care confidence among groups I and, II, I and III, II and III.

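### The 90% power rests on one d and one SD tied to no named sub-scale or contrast; at best it describes education versus control, not CHV versus professional educators

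*Protocol article*

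**What the plan says.** All references are to the protocol article.

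- **Sample size.** The planning effect is given once: "it was expected the mean increase in self-care would be about 22 units (d = 22"). The remaining inputs follow: "Hence to have a power of 90% (σ =40, d = 22, Z α/2 = 1.96, Z β =0.1"). The result is that "minimum 60 participants were needed for each group", and later, after expert advice, "therefore, each group would be included 77 patients". Neither a sub-scale nor a pair of arms is attached to d or σ.
- **Outcomes.** "The self-care components including self-care maintenance, self-care management and self-care confidence would be the main outcome variables of the study". On the metric: "Each sub-scale is standardized to a possible score of zero to 100". No overall self-care score is defined.
- **Primary objectives.** "To compare self-care maintenance, self-care management and self-care confidence among groups I and, II, I and III, II and III". Three sub-scales by three pairs of arms makes nine primary contrasts.
- **Aim and objectives.** The hypothesis is that volunteers do at least as well as professional educators, which concerns group I against group II.
- **Table 1.** Groups I and II both receive education, from the same simplified material. Only group III receives none.

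**The concern.** A power figure has meaning only for a stated outcome and a stated contrast. Here one d and one σ stand beside nine primary contrasts, and the reader cannot tell which of them the 90% describes.

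The gap matters most for I versus II. The plan expects self-care to rise by 22 units. Whether that is a rise after education or a gain over no education, it is the effect of being educated. Both arms in the I-II comparison are educated, so the expected difference between them is something else, and on the study hypothesis it may be close to zero.

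If the 90% is carried over to I-II, a non-significant result could be reported as showing that volunteers match professionals, on the strength of a power the document does not support for that contrast.

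**Working it through.** **Inputs.** From Sample size: d = 22, σ = 40, two-sided 5% (z = 1.96), 90% power, 15% non-response, 77 per group. The standard normal value for 90% power is 1.2816.

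**1. The plan's own figure.** Two-sample formula: n = 2σ²(1.96 + z_β)²/d².

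- 90% power: 2 × (40/22)² × (1.96 + 1.2816)² = 69.5, so 70 per group, or 70/0.85 = 83 with non-response.
- One-sample (before-after) version with SD of change 40: 34.7, so 35, or 42 with non-response.
- Taking the printed Z β of 0.1 literally, two-sample: 2 × (40/22)² × 2.06² = 28.1, so 29.

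None of these gives 60. The two-sample formula does reach 60 at 85% power, or at 80% power with 52 × 1.15 = 60. The shortfall against 90%, the use of β for its quantile, and the same 60 before and after the non-response allowance are separate errors. Correcting them would still leave d and σ unattached to an outcome or contrast. The step is useful here because it suggests that the authors had a between-arm calculation in mind.

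**2. The favourable reading: education versus control on one sub-scale.** Standard error = σ√(2/n). Power = Φ(d/SE − 1.96).

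| n per group | SE | d/SE | Power, d = 22 |
|---|---|---|---|
| 77 | 40 × √(2/77) = 6.45 | 3.41 | 92.7% (92.4% by noncentral t) |
| 65 (77 × 0.85 = 65.45) | 40 × √(2/65) = 7.02 | 3.14 | 88.0% (87.5% by noncentral t) |

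So for I-III or II-III on a single sub-scale, tested at 5% with no adjustment for other contrasts, something near 90% is defensible at the size actually randomised.

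**3. I versus II at the same SD and 77 per group.** The documents give no expected I-II difference. The values 11 (half of 22) and 5 are illustrations.

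- 95% CI half-width: 1.96 × 6.45 = 12.6 points.
- Difference 11: 11/6.45 = 1.71, power about 40%.
- Difference 5: 5/6.45 = 0.78, power about 12%.

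An observed I-II difference of exactly zero would therefore still be compatible with volunteers falling short by 12.6 points, which is 12.6/22 = 57% of the whole gain assumed from education.

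**4. Sensitivity to the SD.** The documents give no sub-scale SD. If it were 20 (assumption), the half-width halves to 6.3 points. Power for a difference of 11 becomes 92.7%, because 11/20 = 22/40, and for a difference of 5 it is 34%. The I-II precision thus depends on the SD. That 22 is not an I-II difference does not.

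**The case against.** The strongest case against is that the section is loosely worded rather than wrong. The primary objectives use self-care as an umbrella term for the three components, so one d and one σ may have been meant for each of them. An increase can mean a gain over control. The section refers to a formula that is not reproduced in the text available to this review and may have shown a two-sample layout. The section never claims 90% power for I-II, and all 231 patients are already allocated.

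Much of this stands, and it rules out three stronger readings that a reader might draw:

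- *A single total score was powered.* An SD of 40 is large for a 0-100 scale, where the maximum is 50, and might suggest a sum of sub-scales. No such score appears in the document, and a large planning SD may simply be cautious.
- *Only a rise over time was powered, which the trial does not analyse.* Only two-sample variants reach 60, which points the other way, and Statistical methods does plan before-after tests in each group.
- *The 90% belongs to no planned comparison.* Step 2 shows that it can fit education versus control.

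What the objection does not meet is I versus II. Under either meaning of increase, and on any sub-scale, 22 is an effect of education. The section does not restrict its power statement, and the hypothesis rests on the one contrast that the statement cannot cover. The missing formula would not by itself supply a sub-scale or a pair of arms.

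**Conclusion.** The concern holds in a limited form. The stated power is tied to no identified sub-scale or contrast. At best it describes I-III or II-III on one sub-scale: about 92% at 77 per group and 88% after 15% loss, if d = 22 and SD 40 are between-arm values on a 0-100 sub-scale and each contrast is tested at an unadjusted two-sided 5%.

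It does not describe I-II. There, at SD 40 and 77 per group, precision is about ±12.6 points, and power is about 40% for a difference of 11 and 12% for 5. Both differences are illustrative, and a smaller SD would improve all three figures. The consequence is for interpretation: a non-significant I-II result would not by itself support the hypothesis that volunteers do at least as well as professionals.

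**What to change.** In Sample size:

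1. Name the sub-scale and the pair of arms to which d = 22 and σ = 40 apply, and state that d is a between-arm difference, if that is what was meant.
2. Restate power at the actual 77 per group, with and without the 15% loss, and limit the claim to education versus control.
3. Drop the 90% for I versus II. Give the expected confidence-interval half-width, or the power for stated differences, separately for that contrast.
4. Say in Statistical methods that a non-significant I-II difference will not be read as equal effectiveness, and that the confidence interval will be reported.

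Keep the sample at 231. The cost is rewording and a short recalculation. The price is a visibly weaker statement for the contrast in the hypothesis.

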#### Implementation

Subjects who met the selection criteria were contacted by a nurse working at the hospital and invited to participate in the study. Those who were available and agreed to participate were recruited to be interviewed. The interviews were conducted by two trained nurses. The completed questionnaires including patients’ names and numbers were sent to the study leader. The list of numbers of those completed a baseline interview were sent to the biostatistician to be randomized as described above. The allocation list provided to the study leader was then used to assign subjects to their group, 77 subjects allocated to group I (exposed to CHVs), 77 subjects to group II (formal health educators) and 77 patients to group III (control group).

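### The sample-size paragraph is wrong as written: Zβ is given the value of β, 60 per group stands both before and after the 15% allowance, and 90% power needs 70 evaluable per group

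*Protocol article*

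**What the plan says.** The protocol article sizes the trial in one short section, Sample size. It takes its effect from an earlier study of similar design: "it was expected the mean increase in self-care would be about 22 units (d = 22"). The inputs and first result follow: "Hence to have a power of 90% (σ =40, d = 22, Z α/2 = 1.96, Z β =0.1) minimum 60 participants were needed" for each group. The next sentence applies the allowance: "Considering a non-response rate of 15%, the sample size for each group would be 60, and total of 180 participants".

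The section then says that everyone who completed the baseline interview and agreed to stay in the study was taken into the trial, 231 patients in all, so that "each group would be included 77 patients". The Implementation section confirms the allocation: "77 subjects allocated to group I (exposed to CHVs), 77 subjects to group II (formal health educators) and 77 patients to group III". No power is stated for 77 per group.

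**The concern.** Three features of the paragraph do not fit together.

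- For 90% power, β is 0.10 and the matching normal quantile Zβ is 1.28. The paragraph gives Zβ the value 0.1.
- Sixty per group is first the minimum needed and then the size once 15% non-response is allowed for. An allowance for loss must raise the number, so the two sentences cannot both be right.
- Sixty does not follow from the stated difference, SD, significance level and power.

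This is the document's only numerical justification of its size. A reader who accepts 90% power at 60 per group will see 77 as a comfortable surplus. If 90% really needs more than 60, that margin is smaller than it looks, which matters when a comparison between two arms shows no clear difference.

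**Working it through.** **Inputs, all from the Sample size section:** d = 22; σ = 40; Zα/2 = 1.96 (two-sided 5%); power 90%; non-response 15%; 60 per group stated; 77 per group randomised.

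**Assumption.** The formula does not appear in the text available. I use the standard formula for comparing two means, which the listed inputs point to:

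n per group = 2σ²(Zα/2 + Zβ)² / d²

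**1. Trying to reproduce 60**

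- Zβ = 0.1 taken literally: 2 × 1600 × (1.96 + 0.1)² / 484 = 28.06, so 29 per group.
- Zβ = 1.2816 (90% power): 2 × 1600 × (1.96 + 1.2816)² / 484 = 69.5, so 70 per group.

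Neither is 60. Other forms at 90% power also miss it:

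| Form | n per group |
|---|---|
| Two means, exact t-test | 71 |
| One-sided 5% (conflicts with the stated 1.96) | 57 |
| One-sample or paired | 35 (37 by t-test) |
| Three-group ANOVA, one group differing by 22 | 64 |

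**2. The 15% allowance**

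- If 60 is the evaluable minimum, recruitment should be 60 / 0.85 = 70.6, so 71 per group.
- If 60 is the recruited number, 60 × 0.85 = 51 remain evaluable.
- From the correct 70 evaluable: 70 / 0.85 = 82.4, so 83 recruited per group.

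**3. Power at the sizes in the plan**

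Power = Φ( d / (σ√(2/n)) − 1.96 )

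| Evaluable per group | How it arises | d / (σ√(2/n)) | Power |
|---|---|---|---|
| 51 | 60 recruited, 15% lost | 2.777 | 79.3% |
| 60 | 60, none lost | 3.012 | 85.4% |
| 65 | 77 randomised, 15% lost (77 × 0.85 = 65.45) | 3.136 | 88.0% |
| 70 | size needed for 90% | 3.254 | 90.2% |
| 77 | 77 randomised, none lost | 3.413 | 92.7% |

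The exact t-test lowers these slightly: 78.5% at 51, 84.8% at 60, 87.5% at 65 and 92.4% at 77. All are for one pairwise comparison at 5% without adjustment for multiple comparisons.

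**The case against.** The strongest reply is that 60 did not set the size of the trial. All 231 available patients were taken, and 77 per group gives 92.7% power with no loss and 88.0% with the plan's own 15% loss, either side of the 90% target. That stands, and it limits the weight of the point. A reader might infer from the faulty arithmetic that the trial is seriously underpowered. On the plan's own inputs it is not.

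A second reply is that the formula is missing, and that a lost subscript could hide a notation meaning Z at β = 0.1. This stands in part. Entering 0.1 literally gives 29, so the text does not show that 0.1 was the number actually used. It may be only a labelling slip. It is still wrong as printed, and neither that error nor the double use of 60 depends on the formula.

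Three further inferences are tempting, and the document does not support them:

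- *That σ = 40 is too large for a 0–100 sub-scale.* It exceeds the SD of a uniform score (100/√12 = 28.9), but that is not an upper bound. The maximum SD on such a scale is 50, and a change score can vary more widely. A smaller SD would also raise power, not lower it.
- *That a before–after increase was misused as a between-group difference.* The use of d cannot be seen without the formula, and the two coincide if the control group does not change.
- *That 60 came from an 80% power calculation inflated by 15%.* The arithmetic comes close (52 × 1.15 = 59.8), but nothing in the text says so.

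**Conclusion.** The sample-size statement is wrong and should be corrected. The value given for Zβ is the value of β, and 60 per group cannot be the size both before and after the allowance. These two conclusions rest on the text alone.

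The size of the error rests on the assumed two-mean formula with d = 22, σ = 40 and two-sided 5%. Ninety per cent power then needs 70 evaluable per group, so the stated minimum is 10 short. Sixty gives about 85% if all are evaluable and about 79% after 15% loss, which is roughly 5 to 11 percentage points below the claim.

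The fault lies in the stated justification. At 77 per group the shortfall against 90% is about 2 points if the full 15% is lost (6 fewer than the 83 needed), and there is none if everyone is followed. The point is one that should be fixed, not one that puts the trial in doubt.

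**What to change.** Rewrite the Sample size paragraph as follows:

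- Give Zβ as 1.28 for 90% power.
- Replace the minimum of 60 with 70 evaluable per group, or about 83 recruited per group at 15% non-response.
- Delete the sentence giving 60 per group (180 in total) after the 15% allowance.
- State that the 77 randomised per group give about 93% power with no loss and about 88% with 15% loss, for one unadjusted pairwise comparison of 22 units at SD 40.

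If the formula actually used was not the two-mean one, name it and give the numbers it yields. The cost is one reworded paragraph and a slightly less favourable power statement. No patients are added and no analysis changes.

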**Figure 1 Fig1:**
[figure not shown]
**The CONSORT flow diagram of the randomized controlled trial.**

### Randomization

#### Sequence generation

The random number list was generated using Microsoft Excel number generator.

#### Allocation concealment mechanism

A registered nurse working at the medical record department at Imam Ali hospital who had collected the list of eligible subjects sent them to the study leader. The study leader provided a biostatistician, who was paid by, but not involved in the study, with the list of names and subject numbers for all 231 subjects. The biostatistician randomized the list, as described above, and then sent the list of names and subject codes with the allocated group to the study leader.

#### Implementation

Subjects who met the selection criteria were contacted by a nurse working at the hospital and invited to participate in the study. Those who were available and agreed to participate were recruited to be interviewed. The interviews were conducted by two trained nurses. The completed questionnaires including patients’ names and numbers were sent to the study leader. The list of numbers of those completed a baseline interview were sent to the biostatistician to be randomized as described above. The allocation list provided to the study leader was then used to assign subjects to their group, 77 subjects allocated to group I (exposed to CHVs), 77 subjects to group II (formal health educators) and 77 patients to group III (control group).

### Blinding

Subjects were aware of where the training took place and who undertook the training and so could have been aware of the group to which they were allocated.

The first data collection occurred prior to randomization. The nurses involved in the data collection undertaken two months after the intervention were recruited to collect the data and has not have further involvement in the study. They were blinded to intervention allocation, but it is possible that the intervention allocation may have become known as a result of discussions during the data collection process.

### Statistical methods

SPSS version 21 and SAS will be used to analyse data. Using descriptive analysis for descriptive data, analytic biostatistics analysis (e.g. ANOVA, independent t-test and paired t-test) for assessing differences (between two groups, among three groups and before and after for each group) will be applied. Regression models will be used to explore associations between predicting factors (e.g. age, gender and education) and self-care scales, and also association between the effectiveness of each strategy and personal characteristics will be used. We will present frequencies and examine the expected associations between different variables to obtain answers for our research questions and hypothesis. T-tests will be used for continuous and normally distributed variables (e.g. self-care maintenance in terms of gender), chi-squared for nominal variables and other proportions (e.g. age group, sex), and multivariate generalized linear regression will be used for detecting associations between outcomes (e.g. self-care management) and explanatory variables (e.g. gender, education and disease duration). Non-parametric tests (e.g., Wilcoxon rank test and Median test) will be used when variables are found not to be normally distributed.

A summary of the interventional strategies is presented in the Table 
1.

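### The baseline pSCHFI score is held for all 231 patients but is not named as a covariate; a baseline-adjusted comparison would be more precise than the tests listed, and the within-arm paired tests should be descriptive only

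*Protocol article*

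**What the plan says.** All references are to the protocol article.

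- **Objective.** The third primary objective is a set of pairwise between-arm comparisons: "To compare self-care maintenance, self-care management and self-care confidence among groups I and, II, I and III, II and III".
- **Timing of the outcome.** Under Outcomes, on the three sub-scales: "These outcomes will be assessed before intervention and two months after intervention". Blinding adds: "The first data collection occurred prior to randomization". Sample size describes the randomised set as "all 231 patients who had completed the primary interviews conducted to obtain the baseline data", so no randomised patient should lack a baseline score.
- **Tests for differences.** Statistical methods lists, introduced as examples, "ANOVA, independent t-test and paired t-test) for assessing differences (between two groups, among three groups and before and after for each group". Non-parametric tests replace these where variables are not normally distributed.
- **Regression.** The same section says "Regression models will be used to explore associations between predicting factors (e.g. age, gender and education) and self-care scales", and later "multivariate generalized linear regression will be used for detecting associations between outcomes (e.g. self-care management) and explanatory variables (e.g. gender, education and disease duration". It also mentions relating the effectiveness of each strategy to personal characteristics. The baseline score is not among the factors named.
- **Target effect.** Sample size: "it was expected the mean increase in self-care would be about 22 units (d = 22", with σ = 40.

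**The concern.** The baseline score is measured on the same scale as the outcome, two months or so earlier, in everyone, before allocation. It is usually the strongest predictor of follow-up that a trial of this kind holds, and using it costs no further data. As written, the tests for arm differences carry no baseline term, and regression is described with personal and disease factors as its examples. Nothing therefore commits the trial to baseline adjustment.

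Two things are at stake.

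1. **Precision.** The study hypothesis is that volunteers are at least as effective as professionals, so the confidence interval for group I against group II has to be narrow enough to inform. The plan also leaves open whether the t-tests and ANOVA use the two-month score or the change from baseline, and these two can differ materially in power.
2. **Interpretation.** Paired before-after tests stand in the same list as the between-arm tests, with no order of importance. A within-arm change mixes any effect of education with regression to the mean and with the effect of being interviewed twice. A significant change in one arm and a non-significant change in another is not a test of the difference between them.

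**Working it through.** **Inputs from the article:** d = 22, σ = 40, two-sided 5% (1.96), 77 per arm, 15% non-response. **Assumed:** r, the correlation between baseline and two-month scores, shown at 0.3, 0.5 and 0.7; equal variance at the two times.

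**Step 1: the plan's own figure.** For two means, n = 2σ²(z_α/2 + z_β)²/d² = 2 × 1600 × (1.96 + 1.2816)²/484 = 69.5, so 70 per group for 90% power. The stated 60 is not reproduced; it gives 85.4%. That is a separate matter, but it means the unadjusted design has less margin than stated. With 77 per arm and all evaluable, unadjusted power is 92.7%. With 15% lost, 77 × 0.85 = 65.45, so about 65 remain and power is 88.0%.

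**Step 2: variance ratios.** With SD σ at both times, the per-patient variances are:
- two-month score: σ²
- change score: 2σ²(1 − r)
- ANCOVA residual: σ²(1 − r²)

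Hence ANCOVA against two-month score = 1 − r². ANCOVA against change = (1 − r²)/[2(1 − r)] = (1 + r)/2.

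| r | vs two-month score | vs change score |
|---|---|---|
| 0.3 | 0.91 | 0.65 |
| 0.5 | 0.75 | 0.75 |
| 0.7 | 0.51 | 0.85 |

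At r = 0.5, 77 per arm is worth 77/0.75 = 102.7 per arm under either alternative.

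**Step 3: power with 65 per arm.** Power = Φ(22/(SD × √(2/65)) − 1.96), with √(2/65) = 0.1754. The article does not say what σ = 40 is the SD of, so both readings are shown.

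- If 40 is the SD of the two-month score, the ANCOVA SD is 40√(1 − r²).
- If 40 is the SD of the change, the ANCOVA SD is 40√((1 + r)/2).

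| r | SD, reading 1 | power | SD, reading 2 | power |
|---|---|---|---|---|
| unadjusted test | 40.0 | 88.0% | 40.0 | 88.0% |
| 0.3 | 38.2 | 90.8% | 32.2 | 97.3% |
| 0.5 | 34.6 | 95.2% | 34.6 | 95.2% |
| 0.7 | 28.6 | 99.2% | 36.9 | 92.5% |

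The unadjusted test is the two-month-score test in reading 1 and the change-score test in reading 2. Worked case, reading 2, r = 0.3: 32.25 × 0.1754 = 5.657; 22/5.657 = 3.889; 3.889 − 1.96 = 1.929; Φ = 0.973.

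**Step 4: why the unstated choice of score matters.** If 40 is the SD at each time and r = 0.3, a change-score test has SD 40√1.4 = 47.3 and, at 77 per arm, power 82.2%. The two-month-score test has 92.7%. ANCOVA has 94.7%.

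**Step 5: paired tests.** Suppose two arms have the same true change and each paired test has 80% power. The chance that exactly one is significant is 2 × 0.8 × 0.2 = 32%; at 50% power it is 2 × 0.5 × 0.5 = 50%. So a split result is common when the arms do not differ.

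**The case against.** The strongest reply is that the article describes a serviceable analysis in condensed form.

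- **The tests and the regression covariates are examples.** This stands. A reader might infer that baseline adjustment is ruled out, or that regression is reserved for personal characteristics. The text says neither: the baseline score is unnamed, not excluded. What remains is that the methods it does attach to arm differences are unadjusted, and that a better one is available free.
- **The unadjusted comparisons are valid.** This stands. Baseline precedes randomisation, so the between-arm tests are unbiased with the right error rate, and chance imbalance is already covered by the standard error. A reader might infer bias; the documents give no ground for it.
- **Baseline may already be used.** The expected effect is described as an increase, which fits change scores. It is therefore too strong to say that the baseline is thrown away. ANCOVA still has the smaller variance in that case, by (1 + r)/2.
- **Misuse of the paired tests is speculative.** A reader might infer that efficacy will be claimed from before-after significance. Nothing says so, and the objectives call for between-arm comparison. The risk comes only from listing both kinds of test without rank.
- **Randomisation.** A reader might take the Excel-generated list to mean simple randomisation and expect larger imbalance. The exact 77/77/77 split does not fit that and suggests an allocation restricted on arm size. The point does not depend on it.

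**Conclusion.** The concern holds as one of efficiency and interpretation, not of validity. ANCOVA on the baseline score has a smaller variance than either reading of the listed tests across the assumed range of r: by 9% to 49% against a two-month-score test, and by 35% to 15% against a change-score test, as r goes from 0.3 to 0.7. With about 65 evaluable per arm, power goes from 88% to between about 91% and 99% under one reading of the SD, and between about 97% and 92.5% under the other.

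The size rests on the assumed r, on equal variance at both times, and on what the SD of 40 refers to. The direction does not depend on which score or which SD is meant. A gain to 99% should not be quoted alone, since it needs both r = 0.7 and the first reading; under the second, the gain shrinks as r rises. If all 77 per arm are evaluable, unadjusted power is already 92.7%, so the benefit is then mainly narrower intervals: on the first reading, the 95% half-width falls from 12.6 to 10.9 units at r = 0.5.

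The paired tests do not answer the pairwise objective and should not carry efficacy conclusions.

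**What to change.** Before outcome data are examined:

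1. State that the main analysis of each sub-scale is a linear model of the two-month score on arm (three levels) and that sub-scale's baseline score.
2. Report the three adjusted pairwise differences (I–II, I–III, II–III) with 95% confidence intervals.
3. Keep the paired before-after tests as description of each arm, and state that no conclusion on efficacy is drawn from them or from comparing their p-values between arms.
4. State how the planned non-parametric fallback relates to this model, for example as a sensitivity analysis.

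No further data are needed, as the baseline interview is complete for all 231 patients. The cost is a revision of the analysis text, with a dated record that the change was made before the two-month results were looked at. That record matters because the article describes a trial already under way.
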